**Fig 2. SPIRIT schedule of enrolment, interventions and assessment.**

** Note: -t2, -t1, baseline (complete measurements twice to get average); t0, post-intervention; t1- t5, 1-week, 1-month, 4-month, 6-month,1-year follow-up.*

1. ***Research background. [usually adopting a four-part structure: (1) Overview of the health problem or research question: definition of the health problem, epidemiological data, etiology, natural history of the disease, disease burden, etc.; (2) Scientific hypothesis: mechanism or principle; (3) Clinical application, for example, treatment studies should explain the treatment methods; (4) Necessity of the study based on current evidence, explaining why this study needs to be conducted]***

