The estimation of Cohen's d is required, with the formula Cohen's d = (δ(Δ) / SDestimate). Referencing studies in similar populations [<https://www.ncbi.nlm.nih.gov/pmc/articles/PMC8939409/>], SDestimate is taken as 250. Therefore, the relevant command is pwr.t.test (d = cohen_d, sig.level = 0.05, power = 0.80, type = "paired", alternative = "two.sided"), resulting in a sample size estimate of 34. Thus, the estimated sample size for the experimental group should be no less than 34 individuals; considering a natural dropout rate of 20%, the sample size for the experimental group should be at least 41 individuals. A ratio of 2:1 will be used to include 20 recreational gamers in the intervention group. A total of 61 participants are required for the intervention group. In order to maintain appropriate comparability, we will recruit an additional 61 participants with matching demographic profiles and equivalent levels of IGD (Internet Gaming Disorder) severity for the control group. Thus, the study demands a cumulative participation of 122 individuals in total.

1. ***Methods of randomization and concealed allocation. [Randomization is used to reduce the risk of selection bias. Methods for generating random number sequences include computer software, random number tables, semi-random or pseudo-random methods (such as using dates, birthdays, or even/odd numbers of hospital visits). Please describe the individuals involved in generating random number sequences and the methods they use. Concealed allocation is used in treatment studies to reduce the risk of selection bias. Key steps in concealed allocation include having a designated person determine the allocation sequence, ensuring that this person is not involved in enrolling participants, and securely storing the allocation table. Please provide detailed descriptions of these steps. Central randomization is a robust method of concealed allocation. Describe the individuals and methods involved in determining the allocation sequence]***

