(1) Primary indicators: average daily gaming time (self-reported by participants), Five Facet Mindfulness Questionnaire (FFMQ), Internet Addiction Test (IAT), Game Craving Scale (adapted from QSU-Brief), Adolescent Executive Functioning Scale (EFS-A), Barratt Impulsiveness Scale, State Mindfulness Scale, Game Craving Visual Analogue Scale, behavioral data, and EEG data (from EEG equipment).

(2) Secondary indicators: Self-Rated Sleep Status Scale, Depression-Anxiety-Stress Scale (DASS-21), Positive and Negative Affect Schedule (PANAS).

(3) Safety indicators: Researchers will inquire daily during the intervention period whether participants experience any adverse reactions. If there are any adverse reactions, they will communicate in person or by phone with the research staff.

Measurement time points are detailed in item 5.

1. ***Definition of Participant Effectiveness Determination. [This includes definitions for participant withdrawal, exclusion, loss to follow-up, confounding factors, study discontinuation, and study suspension]***

(1) Participant Withdrawal: Each participant can withdraw from the study at any time during the experiment without providing any reason. Participants who withdraw voluntarily will not be included in the analysis. Under the conditions of a mixed study, we have a complete access procedure for withdrawn participants. If participants are willing to provide a reason for their withdrawal, it will be recorded by the researchers.

(2) Participant Exclusion: If participants cannot consistently participate in the group interventions during the training process—where the focused breathing meditation training lasts one week—those who attend fewer than 5 sessions will be considered not fully intervened and should theoretically be excluded or adjusted using a mixed-effects model.

(3) Participant Loss to Follow-up: If any participant cannot be contacted for two consecutive attempts after the intervention is completed, they will be classified as lost to follow-up.

(4) Participant Contamination: After the intervention is completed, we will conduct a census of participants. If any participant in the control group attempts to learn about the training methods of the intervention group (or vice versa) and tries to train, they will be classified as contaminated participants.

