8. Insert Active Electrodes: Correspondingly insert the labeled active electrodes into the designated electrode names marked on the EEG cap (make sure to carefully match the electrodes’ labels with the EEG cap). Wrap the CMS and DRL active electrode wires around the other electrodes' cables (3-5 wraps), and plug their connectors into the corresponding matching ports on the amplifier.
9. Confirm Connections and Start Data Collection: After confirming that the EEG software and hardware are properly connected, run the software to collect EEG data. Follow the software usage instructions and ensure the quality of the EEG data meets the required standards before starting the data collection. Save the EEG data to the computer or hard drive according to your naming format.
10. Intervention Content Training Process:

The researchers of this study will collaborate with professional psychological teachers to conduct a week-long intervention content training and multiple training sessions during the follow-up phase.Before each practice session begins, participants will be reminded of the time and location of the practice, and the researchers will conduct on-site check-ins. Training for the intervention content will be provided for one week by the teachers from the Student Mental Health Education and Counseling Center, along with multiple training sessions during the follow-up phase. Professional psychological teachers will guide the training, and the content practiced each day will be sent to the participants' group after each session for continued practice.

1. ***Statistical analysis methods. [Select appropriate statistical analysis methods based on the data type of each measurement variable. Include any additional methods for subgroup analysis or auxiliary analysis. If there are personnel reductions during the trial, indicate whether an intention-to-treat (ITT) analysis was used and compare it with per-protocol (PP) analysis]***

The primary and secondary indicators of this study's scales will be presented to participants in the form of paper questionnaires, while behavioral data and EEG data will be collected from participants using electroencephalography devices.

Demographic data and scale data analysis will use SPSS software, employing t-tests, covariance analysis, etc.; EEG data analysis will utilize Matlab_2013b software, EEGLab software, and scripts.

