For power spectrum and functional connectivity analysis: EEG data will calculate the relative power of six EEG frequency bands at the single electrode and ROI levels (δ: 1-4Hz, θ: 4-8Hz, α: 8-13Hz, low β: 13-20Hz, high β: 20-30Hz, low γ: 30-48Hz). Phase Locking Value (PLV) and Phase Lag Index (PLI) will be calculated using the FieldTrip toolbox. Source localization analysis will be used to explore functional changes in subcortical regions.

For ERP data, we selected the N2 and P3 components based on previous research. The analysis epoch will be 1000ms, with the baseline being the 200ms before stimulus presentation. The N2 negative component is primarily induced by the frontal central region, so the frontal midline electrodes were chosen as the region of interest. The time window for N2 is 250-350ms post-stimulus lock, while P3 is a positive component appearing in the parietal mid/post region, with the parietal electrodes selected as the region of interest, and the time window is 300-400ms post-stimulus presentation. To avoid Type I error rates, we did not analyze individual electrodes; instead, we averaged the amplitude values of the electrodes within the selected time window as the dependent variable for analysis. All work related to ERP component analysis was conducted using ERPLAB.

Finally, we will simultaneously conduct ITT analysis for this study, considering dropout levels as a very important indicator for recording and analysis, attempting to objectively reveal the intervention effects of focused breathing meditation training on executive function from both ITT and PP analysis perspectives..

1. ***Participant management system.***

(1) Contact and Guidance: A contact group composed of relevant researchers is responsible for providing guidance or answers to all research-related content or questions encountered by participants throughout the duration of the study. This ensures that participants have a sufficient understanding of the research and can better cooperate with the process. Researchers must promptly address and record any instances of withdrawal, removal, loss to follow-up, termination, or suspension involving participants.

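### The tests named for scales measured at six post-training visits use only attenders if run visit by visit, so the T1–T5 comparisons would fall short of the promised ITT and could be biased if loss is outcome-related and differs between arms

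*Protocol*

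**What the plan says.** - **Methods.** Under Statistical analysis methods: "Demographic data and scale data analysis will use SPSS software, employing t-tests, covariance analysis, etc". The list is open and covers demographic and scale data. That section names no test for the behavioural task data.
- **ITT.** The same section states: "we will simultaneously conduct ITT analysis for this study, considering dropout levels as a very important indicator for recording and analysis". A per-protocol (PP) analysis is to stand beside it. No rule is given for a missed visit.
- **Visits.** The note to Fig 2 lists "t0, post-intervention; t1- t5, 1-week, 1-month, 4-month, 6-month,1-year follow-up", which makes six post-training visits. Table 1 gives all of them for every primary and secondary scale.
- **Dropout.** Under Sample size estimation: "considering a natural dropout rate of 20%, the sample size for the experimental group should be at least 41 individuals". The rate is tied to no visit.
- **Exclusions.** Under Definition of Participant Effectiveness Determination: "Participants who withdraw voluntarily will not be included in the analysis". Data from suspended participants are also left out of the final analysis. A mixed-effects model appears once, in the same section, as an alternative to excluding people who attend fewer than 5 sessions. It is not offered for missed visits.

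**The concern.** A t-test at a visit needs that visit's value. Covariance analysis at a visit needs that value and the baseline. Someone who completes T0 to T2 and misses the later visits therefore contributes nothing to the later comparisons, although their earlier post-training scores are on file and are informative.

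Two things are at stake. First, the population: a comparison of attenders is not a comparison of everyone randomised, so the named tests do not deliver the promised ITT at T1–T5. Second, bias: if people who did poorly at T0 stop coming in one arm but not in the other, that arm's attenders look better than the arm as randomised. The T0 scores hold the information needed to correct this, and a single-visit test does not use them.

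**Working it through.** **1. The protocol's own dropout figure.** Inputs: d = 125/250 = 0.5, two-sided α = 0.05, power 0.80, paired t-test. The exact calculation gives n = 33.4, rounded up to 34, which reproduces. The figure of 41 reproduces as 34 × 1.2 = 40.8. (Dividing by 0.8 gives 43; that is a separate matter.) With 20% lost, 41 × 0.8 = 32.8 remain of the 41, and 61 × 0.8 = 48.8 of a full arm of 61.

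**2. Assumptions for the bias.** From the protocol: 20% loss and arms of 41 (the IGD participants in the experimental group) or 61 (the full arm). Assumed, because the protocol gives nothing:
- Baseline, T0 and T5 are normal with SD 1 and equal correlation r = 0.5, 0.6 or 0.7; the true effect is zero.
- In one arm, loss before T5 follows a logistic model with log-odds 1.5 per SD of poor T0 score. In the other arm, loss is random. Both lose 20%.

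**3. Approximate formula.** Let s be the shift in mean T0 score among attenders of the affected arm, s = E[Z(1 − p(Z))]/0.8, where p is the loss probability set to average 0.20. Numerically, s = 0.227 SD towards better scores.
- t-test bias at T5 = r·s
- Covariance-analysis bias at T5 ≈ r·s − r·(r·s) = r(1 − r)·s

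| r | t-test, r·s | covariance analysis, r(1 − r)·s |
|---|---|---|
| 0.5 | 0.113 | 0.057 |
| 0.6 | 0.136 | 0.054 |
| 0.7 | 0.159 | 0.048 |

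**4. Simulation of the same setting** (6,000 replicates per row; bias in SD towards the affected arm):

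| n per arm | r | t-test bias | type I | covariance bias | type I | bias using T0 |
|---|---|---|---|---|---|---|
| 41 | 0.5 | 0.110 | 7.5% | 0.056 | 5.3% | 0.00 |
| 41 | 0.6 | 0.139 | 8.3% | 0.058 | 6.2% | 0.00 |
| 41 | 0.7 | 0.151 | 9.9% | 0.047 | 5.7% | 0.00 |
| 61 | 0.5 | 0.116 | 9.8% | 0.060 | 7.2% | 0.00 |
| 61 | 0.6 | 0.133 | 9.8% | 0.055 | 6.6% | 0.00 |
| 61 | 0.7 | 0.158 | 12.8% | 0.050 | 6.4% | 0.00 |

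Monte Carlo error on the rejection rates is about 0.3–0.4 percentage points, so the top of the t-test range is best read as about 12%. The last column is a likelihood estimate that also uses the T0 scores of those who missed T5.

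**5. When there is no bias.** With random loss in both arms, or log-odds 1.5 per SD in both arms, every estimate is within 0.01 SD of zero and type I error is about 5%.

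**The case against.** The strongest reply is that the protocol does not fix a completers' analysis. The list of methods is left open, names no visit or endpoint, and does not rule out a repeated-measures form of covariance analysis. The ITT promise does not rule out imputation, and rules for missing visits may sit in a statistical analysis plan that is not shown. This stands as a limit. A reader might infer that the promised ITT result is already a completers' result, or that it will favour mindfulness; the text supports neither. What survives is narrower. The protocol does choose methods, and the ones it names do not fit its own six-visit schedule and ITT promise if run visit by visit. Its only mixed model is for low attendance.

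The second reply is that the figures rest on an assumed one-sided mechanism. This also stands. The Fig 3 legend gives the mindfulness arm daily audio-guided practice and the control arm none after training, and the trial is not double-blind. Different loss is therefore plausible, but not established. A 20% dropout by itself causes no bias.

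Two further limits hold. It is tempting to convert the bias to milliseconds of Stroop reaction time, but the sentence on tests covers scales, not task data. And at T0 there is no earlier post-training value to recover, so the argument concerns T1–T5 only.

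Finally, the rules that drop withdrawn and suspended participants conflict with ITT more directly than the choice of test. That is true, and a mixed model would not help people whom those rules remove first. Lifting the rules would still leave visit-wise tests discarding people who simply miss a visit, so both need changing.

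**Conclusion.** The point holds in this limited form: the named tests, applied at each visit, do not provide the promised ITT comparison at T1–T5. Under the one-sided mechanism assumed above, bias at T5 is about 0.05–0.06 SD for covariance analysis, with type I error about 5–7%, and about 0.11–0.16 SD for t-tests, with type I error about 7–12%. For covariance analysis this is about a quarter to a third of a standard error (0.14–0.21 SD in these runs), which is modest. If loss is random, or follows the same mechanism in both arms, bias is about zero. The case for change is that a better-suited method is cheap and uses data already collected, not that the result is known to be wrong.

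**What to change.** 1. For the repeated scale outcomes, make the ITT analysis one linear mixed model for repeated measures over T0–T5, with arm, visit, arm-by-visit and baseline. Include every randomised participant with any post-training value, and read the arm difference at each visit from this model.
2. Keep the data that withdrawn and suspended participants have already given. Confine the exclusions under Definition of Participant Effectiveness Determination to the PP analysis. Without this step the model cannot do its work.
3. Use the same model for the task data, for which no test is named.
4. Keep the visit-wise t-tests and covariance analyses as a check, and add a simple missing-not-at-random sensitivity analysis. Report how many randomised participants have no post-training value, since the model does not include them.
5. Name a fallback covariance structure in advance. An unstructured matrix over six visits has 6 × 7/2 = 21 parameters and may not converge with arms of this size.

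The cost is a change of wording and a standard mixed-model procedure in SPSS, the software already named; no new data are needed. The drawbacks are that the model assumes data missing at random (a weaker assumption than the visit-wise tests make) and that it gives essentially no correction at T0.

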1. ***Plan for Sharing Raw Data. [Describe the plan for sharing raw data with the public. Specify the maximum time frame for sharing data, which should not exceed 6 months after the end of the trial. Explain the public platform that will be used for data sharing]***

The raw data will be uploaded to the ResMan Clinical Trial Public Management Platform, http://www.medresman.org.cn.

1. ***Treatment and Management of Participants after the Trial Ends. [Describe how participants who have not experienced improvement in their condition at the end of the trial will continue to receive medical care. Explain the measures that will be taken to ensure their ongoing treatment and management]***

Since the participants included in this study are all healthy university students and are guided by professional instructors in focused breathing meditation training, this training aims to explore the effects of a brief mindfulness intervention on executive function. Additionally, this process can help participants enhance their ability to self-regulate emotions when facing various stressors in real life. If, after the experiment, it is found that any participant's stress level reaches a clinically significant threshold, a psychological counselor from the university's psychological center will provide active intervention and, if necessary, refer them to nearby specialized hospitals for further support.

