According to the latest data from the China Internet Network Information Center [[1](#_ENREF_1" \o "Center, 2022 #684)], by June 2022, the scale of online game users in our country still exceeded half of the total internet user base, reaching 552 million, among whom mobile games dominated, accounting for 60.9% of underage gamers [[2](#_ENREF_2" \o "Center, 2021 #685)]. Unlike substance addiction, which is induced by addictive substances, internet gaming disorder (IGD) is considered a behavioral addiction, characterized prominently by uncontrollable gaming behavior leading to emotional distress, neglect of academic or life responsibilities, and damage to interpersonal relationships, causing serious negative impacts on both individuals and society [[3](#_ENREF_3" \o "Ko, 2020 #686)]. According to the dual-process model, cognitive-behavioral model, and I-PACE model in addiction theory, it is concluded that emotional and cognitive mechanisms jointly contribute to the development and maintenance of gaming addiction, with cue-induced craving and diminished executive function closely related to IGD. Executive function regulation is also required for cue-induced craving, making executive function a critical area of research in IGD. The primary behavioral diagnostic feature of IGD is excessive gaming behavior despite the negative consequences, and behind this behavioral dysfunction lies functional impairment. Studies using fMRI on individuals with IGD have found abnormalities in brain structures such as the dorsolateral prefrontal cortex, anterior cingulate cortex, and orbitofrontal cortex, areas closely associated with executive function. However, studies on the executive function of IGD individuals have mainly focused on the subcomponent of inhibitory control, with less attention given to switching and updating components, particularly regarding the cognitive flexibility represented by switching, which remains controversial in the field of internet gaming addiction. To better explore the neurobiological mechanisms related to internet gaming addiction, it is necessary to investigate all three subcomponents of executive function.

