Mindfulness, as an effective addiction treatment approach, has been widely applied in interventions for addiction and relapse, improving craving and maladaptive cognition in individuals with IGD [[4](#_ENREF_4" \o "Li, 2017 #687)], and has been proven to significantly enhance prefrontal cortex function, which is closely related to executive function. Individuals can improve overall executive function by initiating attention monitoring processes, strengthening working memory, and increasing cognitive flexibility in task switching, thus reducing impulsivity and addictive behaviors. Research on mindfulness interventions concerning executive function has primarily targeted populations such as patients with brain injuries, children with underdeveloped brain mechanisms, and elderly individuals with declining brain functions; there is less research on normally developed, healthy adults, especially within the addicted population, where the focus has largely been on smokers rather than individuals with IGD. Moreover, due to the time-consuming nature and face-to-face requirements of mindfulness interventions, the demand for short-term self-guided practices has increased. Existing research has confirmed that single-session and five-minute brief mindfulness interventions can improve health outcomes.

Currently, whether the three subcomponents of executive function in individuals with IGD are impaired, and whether mindfulness interventions can improve executive function and related brain mechanisms in IGD populations and normal healthy populations, lacks sufficient in-depth investigation. This study proposes to use a randomized controlled trial design to explore the effects of a one-week focused breathing meditation practice on executive function. On one hand, this may address the issue of low acceptance due to the long duration of mindfulness interventions, and on the other hand, exploring brain function mechanisms could provide more targeted intervention strategies for executive function research.

1. ***Objective***

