Through the use of scales, behavioral data, and EEG data, this study aims to investigate whether the three sub-components of executive function in individuals with internet gaming addiction are impaired. Furthermore, it will conduct a one-week focused breathing meditation intervention to explore the effectiveness of concise mindfulness on executive function and its impact on brain function mechanisms. This endeavor will provide more targeted intervention strategies for research into executive function.

1. ***Inclusion and exclusion criteria. [Inclusion criteria define the main body of the study and determine the representativeness of the study population; exclusion criteria define individuals within the study population that may affect the study and determine the homogeneity of the study population]***

Inclusion criteria:

(1) Right-handedness;

(2) Normal vision or corrected-to-normal vision;

(3) Age between 18 and 40 years;

(4) Good mental and physical health (PHQ-9 total score < 20, GAD-7 total score < 11);

(5) Absence of other addictions (e.g., smoking, alcohol, gambling);

(6) For individuals with internet gaming disorder (IGD): Internet Addiction Test (IAT) score ≥ 50, DSM-5 score ≥ 5, gaming history exceeding 2 years, and gaming time of more than 14 hours per week;

(7) For recreational gamers: IAT score < 50, DSM-5 score < 5.

Exclusion criteria:

(1) Individuals with asthma, epilepsy, or a history of mental illness;

(2) Those who have taken steroid medications within the past three months;

(3) Individuals who have practiced meditation, yoga, Tai Chi, or Qi Gong for more than 20 hours in the past year or throughout their lifetime, attended meditation or yoga retreats, or participated in any meditation courses;

(4) Individuals unsuitable for electroencephalogram (EEG) testing due to metal implants, severe head injuries, contact dermatitis, or silicone allergies;

(5) Those with a PHQ-9 total score ≥ 20 or a GAD-7 total score ≥ 11;

(6) Individuals with other addictions (such as smoking, alcohol, or gambling);

(7) Individuals with strong adherence to a particular religious belief that would interfere with their ability to participate in the required meditation exercises;

(8) Individuals currently participating in similar trials or other neurophysiological studies.

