(2) Emergency Team: Comprised of researchers and psychological teachers from the university's mental health education center, this team will timely identify and intervene in cases of adverse reactions experienced by participants during the study. In situations that cannot be resolved, they will provide additional channels for addressing the issues faced by those participants. Every participant is encouraged and expected to proactively reach out to members of this team if they encounter any health-related problems at any time.

(3) Confidentiality of Information: Any information and data obtained about participants during the study will be kept strictly confidential. Information that could identify participants will not be disclosed to anyone outside the research team without the participant's consent. Any public reports related to the results of this research will not disclose the personal identities of the participants.

1. ***Specimen management system. [This includes the processes and systems for specimen collection, storage, and submission]***

This study does not involve the collection of samples.

1. ***Drug and equipment management system. [This includes the storage and distribution processes, checking systems, use, and recovery of drugs and equipment]***

This study does not involve the use of drugs or equipment management.

1. ***Data management system. [This includes data collection, management of source data and files, personnel responsible for data collection and entry, and checking systems]***

Before statistical processing, all collected data from participants will be uniformly anonymized, and measures such as data encryption or other secure storage methods will be implemented.

(1) Data Collection: Relevant data will be collected strictly in accordance with the standard operating procedures for different data collection methods.

(2) Management of Source Data and Files: Source data will be stored on the appropriate data platform, and multiple backups of the files will be created (such as storing them on a specialized, non-networked hard drive or an external hard drive used for data analysis). For some original data stored on third-party online platforms, timely downloads and secure storage will be conducted to ensure network security, enhance endpoint protection, prevent information leakage, maintain software and data backups, and regularly check for vulnerabilities and prevent virus intrusions.

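### Post-trial counselling or referral is triggered only by stress, so an IGD participant whose gaming problem persists at one year with ordinary stress must ask for help

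*Protocol*

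**What the plan says.** The template prompt under the Protocol heading on treatment and management after the trial ends asks how people whose condition has not improved will go on receiving care. The answer begins "Since the participants included in this study are all healthy university students" and describes the training. It then gives one condition for action: if a participant's "stress level reaches a clinically significant threshold", a counsellor from the university's psychological centre steps in and can refer to a specialised hospital. Gaming disorder is not mentioned.

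Elsewhere the Protocol says:

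- **Research background:** IGD is a behavioural addiction "causing serious negative impacts on both individuals and society".
- **Inclusion criterion (6):** IGD participants need an IAT score of at least 50 plus "DSM-5 score ≥ 5, gaming history exceeding 2 years, and gaming time of more than 14 hours per week".
- **Inclusion criterion (4), for everyone:** "Good mental and physical health (PHQ-9 total score < 20, GAD-7 total score < 11".
- **Exclusion criterion (1), for everyone:** "Individuals with asthma, epilepsy, or a history of mental illness".
- **Participant management system, (2) Emergency Team:** "Every participant is encouraged and expected to proactively reach out to members of this team if they encounter any health-related problems at any time".

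**The concern.** The section exists to cover participants who have not improved, and the condition under study is IGD. Yet the only event that makes the study team act is stress. A participant can finish the year with an IAT score still in the range that qualified them for the trial and, if stress is ordinary, nobody is asked to approach them. The team will hold that score. The Protocol itself describes IGD as uncontrollable gaming with neglect of responsibilities, so relying on such a person to seek help is a weak safeguard. What is at stake is participant care after close-out.

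**Working it through.** **Step 1. Which care routes exist, and what sets each one off?**

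| Protocol section | What sets it off | Reaches persistent IGD with ordinary stress? |
|---|---|---|
| Treatment and management after the trial ends | Clinically significant stress | No |
| Participant effectiveness determination, (5) termination | An adverse event | No; an unimproved condition is not an adverse event |
| Adverse events and reactions | A reported adverse event, or a bad reaction during EEG recording | No |
| Emergency Team, active duty | An adverse reaction during the study | No |
| Emergency Team, open invitation | The participant makes contact | Yes, but only if the participant asks |
| Intervention content training process | Scheduled sessions in the follow-up phase | No; part of the trial, not an offer after it |

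Team-initiated routes after the trial: one, on stress. Team-initiated routes on IAT or gaming time: none.

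**Step 2. Does the team hold the data to do better?** Table 1 and the list of observation items schedule IAT and average daily gaming time through T5 (one year). The DSM-5 criteria are scheduled at -T1 only. At T5 the team can therefore see whether IAT is still at or above 50, but cannot show that the full entry definition is still met. IAT can prompt an offer; it cannot confirm a diagnosis.

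**Step 3. How many people could this concern?** Inputs are from the sample size section. The plan's own figures reproduce:

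- d = 125/250 = 0.5; paired t-test, two-sided 5%, power 80%: n = 33.37, rounded up to 34.
- 34 × 1.2 = 40.8, so 41.
- 41 + 20 recreational gamers = 61 in the intervention group; 2 × 61 = 122 in total.

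Ceilings follow:

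- IGD share of the intervention group: 61 − 20 = 41; 41/61 = 67%.
- IGD participants remaining at T5 with 20% dropout: 0.8 × 41 = 32.8, about 33.
- If controls have the same mix: 2 × 41 = 82 of 122 (67%); 0.8 × 82 = 65.6, about 66.

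The same mix in the control group is an assumption. The sample size section says controls are matched on demographics and IGD severity, but gives no count of IGD controls. The floor is 0 in each case, because the documents do not say how many will keep a high IAT score with ordinary stress.

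**The case against.** **The word healthy.** A reader might infer that calling all participants healthy flatly contradicts enrolling people for IGD, especially as the Research background sets effects "in IGD populations and normal healthy populations" side by side. The documents do not support so strong a reading. Criterion (4) and exclusion (1) apply to everyone, so the word fits the eligibility screens. An earlier paragraph of the same background treats people with addiction as a group within healthy adults. This objection stands, and the wording is loose rather than contradictory. It does not rescue the care rule, since those screens concern other problems and supply no route for persistent gaming disorder.

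**What the documents can show.** A reader might also infer that the trial makes no offer anywhere. The ethics section confirms a paper consent form, which is not among the documents at hand and may describe care after the trial. The point therefore covers the visible protocol only.

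**The open route.** The invitation to contact the emergency team is not limited to stress or adverse events, and that team includes psychology teachers from the university. This stands and narrows the gap: the difference is between help the participant must request and help the team offers.

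**The threshold.** An IAT score of 50 is an enrolment cut-off, not an established care threshold, and the DSM-5 criteria are not repeated. This also stands. It is why the score should only prompt an offer, with a counsellor judging need.

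**The size.** A range that starts at zero is not evidence of harm. Agreed; the upper figures bound the workload of the fix and do not estimate people harmed.

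**Conclusion.** The point holds as a minor participant-care correction. In the visible protocol, the section meant for participants who have not improved makes stress its only trigger. An IGD participant in either arm whose problem persists at T5 with ordinary stress is left to self-initiated contact. The number is unknown: 0 to about 33 in the intervention group, and 0 to about 66 overall if controls mirror its mix, both with the planned 20% dropout. Nothing here alters the primary comparison, the error rates or the trial's conclusions, and it should not be read as a flaw in the evidence the trial will produce.

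**What to change.** Make two edits to the section on treatment and management after the trial ends.

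1. Qualify the opening description, for example: participants are university students without other mental or physical illness.
2. Add: any participant enrolled as IGD, in either arm, whose IAT score is still 50 or higher at T5 will be offered the same university counselling and, if necessary, referral; the counsellor will judge need.

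Use IAT alone as the prompt. Also requiring gaming time above the entry level (14 hours a week, or 14/7 = 2 hours a day) would miss someone with a high IAT score who reports 1.9 hours a day.

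No new scheduled measurement is needed, because IAT is already collected at T5 and the counselling and referral route already exists. The existing stress rule already requires linking a score to a person, so this adds no new kind of data handling. The cost is the counsellor's time for added offers: number unknown, at most about 66 under the assumptions above.
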